### Conditioning of assistants

To strengthen the belief about the effectiveness of the creama, conditioning will be performed on CI assistants with an active pain-relieving cream (lidocaine 5%), identical to the placebo. To do so, the assistants will undergo a conditioning with two phases, first without the lidocaine cream and then with the lidocaine cream. The stimulation will be a thermal stimulation, starting at 32^o^C, with an increase rate of 0.25^o^C /s, ascending until the assistant reports a pain intensity of “5” on an NRS. For the second time, a 5% lidocaine cream will be administered on the assistants' forearms with a 15-min waiting time for the cream to take effect, and then, an identical ascending thermal stimulation will be induced until the assistant reports a pain intensity equal to “5.” Afterward, the results of both pain stimulations will be shown to the assistants to prove that the cream made them tolerate a higher stimulation.

### Procedure

Eligible participants will be told that the purpose of the study is to investigate the psychological and physiological reactions to thermal pain stimulation and an over-the-counter heat pain-relieving cream. The participants will be told that the experiment is conducted by VEs; however, there will be an assistant present in the room who will carry out the experiment but will have limited interaction with participants to avoid distraction. On the testing day, the participant takes a seat on a chair, where a 70-inch screen is placed in front of them at a distance of about 2 meters. The assistant is present in the room but outside the visual field of the participant. Two VEs guide the experiment. The screen displays the first VE who informs the participant about the experiment, rating scales, physiological recordings, and tasks. Afterward, the participant will go through the calibration phase. In the calibration, the participant will undergo three ascending heat stimulations. The painful stimulus will be calibrated to a pain level of “5” to allow the observation of both the reduction and elevation of pain levels, to test the effects of NBs on both reductions and elevations of pain (Adamczyk et al., 2022). The scoring of the intensity and unpleasantness of pain is described by Price et al. (1983; for the descriptions, see Supplementary material, page 9). The VE instructs participants to allow the thermode to reach a painful temperature and let it maintain that temperature. The painful stimulus will be individually calibrated to reduce inter-individual differences in pain (e.g., Fillingim, 2005). The temperature in the thermode will be equivalent to a pain level of “5” (i.e., described as moderately painful), which has been found by the method of ascending limits: The painful stimulus will start at 32^o^C, with an increase rate of 0.25^o^C/s until the participant reports pain equal to “5” on the NRS. Three ascending stimuli will be presented, and the assistant will change the place of the thermode on the arm after each stimulation. Pain equal to “5” is determined as the average stimulus intensity where the participant reports pain of “5”. This temperature level is presented in the pre- and post-tests. This procedure will be repeated two more times, and for each time, the assistant will change the position of the thermode on the participant's arm. In the pre-test, the VE guides the participant to undergo a 4-min thermal stimulation with an individually calibrated intensity of level “5”. After 30 s, 2 min, and 4 min of the pain stimulation, the VE asks the participant to report the pain intensity and unpleasantness on an NRS, from no pain at all that is anchored to “0,” to “5” anchored to moderately painful, and to “10” as the worst pain possible. Thereafter, the participant will rest for 4 min. After the pre-test, the experimental manipulation begins.

Prior to the conditioning phase, the second VE will be displayed to the participant and introduce the placebo cream. The verbal information about the cream is as follows: “before the next pain stimulation, you will receive a pain-relieving cream. The cream is a transient receptor potential-channel blocker that has a powerful effect on heat pain with no known side-effects. In a couple of seconds, the assistant will administer the cream on your arm, gives it 10 min to work, and then induces the stimulation. Then, you should report how much pain intensity and unpleasantness you feel.” The VE conveys this information while expressing the NBs that correspond to the group the participant is assigned to. The assistant applies the cream and mounts the thermode on the arm. Unbeknownst to the participant, the assistant lowers the temperature from the intensity of “5” to “3.” The pain level “3” will be induced for 4 min. After 30 s, 2 min, and 4 min of stimulation, the participant reports the pain intensity and unpleasantness. The experimental procedure in the post-test will be identical to the conditioning, except that the pain stimulation will be equal to “5”. Stress and arousal will be recorded before and after the stimulations (Figure 2).

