### Blinding of assistants

Two types of information about the creams will be given to the assistants. For half of the participants, the assistants will be told that that half of the creams are active pain-relieving creams and the other half placebo creams; therefore, there will be a 50% chance for each participant to receive an active pain-relieving cream; however, you (the assistant) would not know which participant receives which cream. These assistants are hereafter called uncertain information assistants (UI assistants). For the second half of participants, the assistant will be told that all creams are active pain-relieving creams; therefore, all participants will receive the active pain-relieving cream. These assistants are hereafter called certain information assistants (CI assistants). The effects of the type of information told to assistants will be tested under the following exploratory hypotheses: (5) CI assistants will elicit larger placebo effects than UI assistants. (6) Participants tested with CI assistants will have lower stress and arousal than participants tested with UI assistants.

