In this experiment, all groups will receive a placebo treatment and verbal suggestions about the treatment. As there is no control group with no treatment in this design, we may not be able to exclude the reduction in pain to a placebo effect (Flaten et al., 2013). However, this design was chosen because the aim of the study was to investigate the effects of caregivers' NBs on pain reports and placebo effects. To test the effects of a factor on placebo effects, previous studies have used similar designs with no natural history control group (Flaten et al., 2006; Dutt-Gupta et al., 2007; Varelmann et al., 2010). As all groups will receive treatment plus verbal suggestions, a reduction in pain is expected in all groups. The NBs of the videotaped experimenters are the only factor that is different between the groups; thus, any difference in the reduced pain between the groups can be attributed to the non-verbal manipulations.

To strengthen the placebo effects, a conditioning procedure was also added. It has been shown that verbal suggestion about a treatment plus conditioning can enhance the generation of placebo effects (e.g., Colloca et al., 2008; Flaten et al., 2013).

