## Expected limitations

Several challenges exist in conducting this experiment. First is the use of VEs, which hinder the transmission of emotions to participants. Moreover, using a videotaped caregiver will be less ecologically valid than using a real-life person. However, the use of VEs provided the highest level of control over the NB of the caregivers, and as a trade-off, this decreased the transmission of positive expectations and emotions to participants, even though previous studies reported a successful use of videotape caregivers in their experiments (e.g., Ruben et al., 2017; van Osch et al., 2017). Second, even though the assistants in the room will receive training to control their verbal and non-verbal interactions with the participants, there is still a chance that their presence affects the results (e.g., Gracely et al., 1985; Kaptchuk, 2001). However, the assistants will be given two types of information about the cream, and the effects of the assistants' information will be analyzed. Third, the expression of an emotion cannot be found in just one single NB, and oftentimes emotions are expressed through a combination of NBs (Matsumoto, 2006a). However, we did not separate the NBs but enhanced the amplitude of one or two NBs more than the others. Fourth, we proposed comparing the positively enhanced NBs with a condition with neutral NBs. Even though our preparatory study supported the validity of both the positively enhanced and the neutral conditions, the neutral conditions may still elicit emotions, as there is no true neutral NB. To partly control for the negativity effects, each participant will have two VEs, one playing the phases with neutral NBs (phases before conditioning), and the second VE playing the positively enhanced conditions (i.e., conditioning and the post-test). Fifth, along with the NB that was intentionally enhanced, some other NBs were enhanced; however, the NB of the focus was still with the highest amplitude. Furthermore, the analyses showed that the actors differed in physical attractiveness, and this could confound the effects of NBs. As mentioned before, to control for the effects of attractiveness, two actors with the higher and lower ratings of physical attractiveness will be used in each NB group. This approach may control for the confounding effects of attractiveness in the NBs. We only tested the impressions of positivity, dominance and being in charge, and expressivity. However, the combination of the manipulated NBs might have produced other impressions. Lastly, having only female actors limits the generalizability of our findings to providers of other genders.

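### No masking of the in-room assistant to the non-verbal-behaviour arm is described, so crediting every group difference to the videotaped experimenters is not secured

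*Protocol article*

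**What the plan says.** Under Procedure, participants are told that "there will be an assistant present in the room who will carry out the experiment", with little contact so as not to distract them. The assistant's position is also given: "The assistant is present in the room but outside the visual field of the participant". The Figure 2 legend places randomisation after the pre-test. VE2 then presents the cream: "The VE conveys this information while expressing the NBs that correspond to the group the participant is assigned to". Next, "The assistant applies the cream and mounts the thermode on the arm", and in the conditioning phase "the assistant lowers the temperature from the intensity of" level 5 to level 3. The post-test repeats these steps at level 5, and Expected limitations confirms that VE2 plays both phases.

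Blinding of assistants opens with "Two types of information about the creams will be given to the assistants" and deals only with that. Assistants are told either that half the creams are active (uncertain information, UI) or that all are (certain information, CI). The Design section enters CI/UI as a covariate. Research assistants describes written instructions, training in controlling their own behaviour, and a simulation run before testing starts.

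The General discussion states: "The NBs of the videotaped experimenters are the only factor that is different between the groups". It concludes that whatever difference in pain reduction appears between groups may be credited to the manipulated behaviours. Expected limitations concedes that, even with training, "there is still a chance that their presence affects the results", and offers analysis of the cream information in response.

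**The concern.** The randomised comparison is between NB arms. An assistant who recognises the arm may act more warmly or confidently in one arm than in another, or may be affected by the video in the same way as the participant. Any such live effect on the participant would be counted as an effect of the videotaped behaviour.

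The trial's own reasoning makes this route plausible. Exploratory hypotheses 5 and 6 predict that what assistants believe about the cream changes participants' placebo response, stress and arousal. A plan that expects one kind of assistant belief to reach the participant cannot take for granted that awareness of the NB arm does not. What is at stake is the main inference: whether a difference between arms belongs to the video alone.

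**Working it through.** The plan gives no figure on this point, so the check sets the sections side by side.

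**1. When could the arm influence the assistant?** Calibration and the pre-test come before randomisation and use only neutral footage. All arm-specific exposure falls in conditioning and the post-test. The analysed outcome is the post-test minus pre-test change, so an arm-dependent assistant effect at post-test would enter the change score in full, with nothing at pre-test to offset it.

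**2. Can the assistant tell the arm?** The article does not state the assistant's view of the screen, the audio set-up or who starts the video. It does say that the assistant is in the room, and VE2's script announces that the assistant is about to apply the cream, so the assistant's actions are timed to the video. The arms differ as follows:

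- Positive tone of voice is defined by sound. Coders rated it from audio alone (Procedure for coding) and gave it the highest positivity in tone (Construct validity of the manipulated NB conditions). A listener could probably recognise it.
- Positive facial expression and positive body movement are defined mainly by what is seen (NB scenarios). Both were rated above neutral for tone, but with picture and sound played together, so those ratings do not show that sound alone separates them from neutral.

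Partial knowledge by ear is therefore likely. Full knowledge would need sight of the screen or control of the video file.

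**3. Do the stated safeguards reach this route?** Write the expected change score in arm g at cream-information level c as

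E(g, c) = μ + V(g) + A(g) + I(c),

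where V is the video effect, A the effect of an assistant reacting to the arm, and I the effect of the CI/UI information. The contrast with the neutral condition (NC) at the same c is

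E(g, c) − E(NC, c) = [V(g) − V(NC)] + [A(g) − A(NC)].

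The CI/UI term cancels and the assistant term does not. A covariate for what assistants were told about the cream cannot absorb behaviour that varies with NB arm. Training may make A smaller, but it is general, and Expected limitations itself does not treat it as sufficient.

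**4. Does the attribution follow?** Crediting the whole contrast to the video requires A(g) = A(NC) for every arm. No section states or secures this.

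**The case against.** The strongest reply is that the premise is an inference. Nothing in the article says that the assistant hears or sees VE2, and a journal article condenses a fuller protocol that may describe masking. This stands as a limit on the claim: what can be said is that no masking is described and that partial knowledge is likely. It does not remove the point, because the article has a section on assistant blinding and another on limitations, and neither mentions the NB arm.

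A reader might infer that the assistant knows every arm, or that the bias favours positive facial expression, the arm expected to do best. The documents support neither. If sound is the route, positive tone of voice is the most recognisable arm, and bias in its favour would work against the hypothesis that facial expression is best. Bias towards facial expression would need sight of the screen and probably knowledge of the hypotheses; the article states neither for the assistants.

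A reader might also say that the General discussion is flatly contradicted. That is too strong. The sentence describes what is manipulated, in a paragraph explaining why there is no untreated group. A possible route for performance bias is not a second stated difference, and the limitations section openly lists the assistants' presence.

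The existing controls also deserve weight. Assistants are trained and must pass a simulation, they stay out of sight with little contact, and in the pre-test the videotaped experimenter asks for the ratings. The level-5 temperature is fixed by calibration before randomisation, and the planned steps are the same in every arm. These reduce the room for bias; none makes the assistant unaware of the arm.

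**Conclusion.** The point holds in a limited form. As described, the plan leaves open a route for arm-dependent performance bias that neither the training nor the CI/UI analysis closes. The unqualified attribution in the General discussion is not secured by the design and sits in tension with Expected limitations.

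The size is unknown. The documents give no figure from which to estimate it. The only effect quoted under Statistical power compares natural history with placebo in another study and is not a yardstick for an assistant effect. The direction is also unknown.

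The conclusion assumes that an assistant in the room during VE2's presentation perceives at least some of it, and that the full protocol contains no masking step left out of the article.

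**What to change.** - Start VE2 from coded files, so that operating the video does not reveal the arm.
- Place the assistant without sight of the screen.
- Do not tell assistants the NB hypotheses.
- Record each assistant's guess of the arm after each session, and report the guesses by arm.
- If sound masking is added, limit it to VE2's introduction of the cream. It should not be used during stimulation, when the assistant must be able to hear the participant.
- State in the protocol whether assistants can see or hear VE2.
- In any case, qualify the General discussion to say that group differences may include the reaction of an assistant aware of the arm.

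The cost is slightly more set-up and one extra item recorded per session. Some unblinding by sound will remain, particularly for positive tone of voice; the recorded guesses will show how much. The rewording costs nothing.

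### Assistants who are meant to believe in the cream lower the heat themselves, and no belief check is described, so a null certain- versus uncertain-information result could not be interpreted

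*Protocol article*

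**What the plan says.** Under Blinding of assistants (Protocol article), assistants receive one of two messages. For one half of participants they hear that "there will be a 50% chance for each participant to receive an active pain-relieving cream". For the other half, "the assistant will be told that all creams are active pain-relieving creams". Hypothesis 5 is that "CI assistants will elicit larger placebo effects than UI assistants"; hypothesis 6 expects lower stress and arousal with CI assistants. Both are labelled exploratory.

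Conditioning of assistants adds a demonstration for one side only: "conditioning will be performed on CI assistants with an active pain-relieving cream (lidocaine 5%), identical to the placebo". The assistant receives the same ascending heat without and then with lidocaine, and is shown both results as proof that the cream works.

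The Procedure section then describes the participant's conditioning phase. The assistant applies the cream and mounts the thermode, and "Unbeknownst to the participant, the assistant lowers the temperature from the intensity of" 5 to 3. The post-test returns to 5. The step is written for the assistant in general, with no distinction between CI and UI.

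The Design section carries assistants' knowledge as a two-level covariate. Expected limitations concedes that the assistants' presence may affect results and answers this with the planned analysis of the information given to them. It does not mention that the assistants know about the lowered heat.

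**The concern.** The CI/UI manipulation depends on what the assistant believes while she is testing. The lidocaine demonstration persuades her by holding the heat procedure constant and changing only the cream. In the participant's conditioning phase she then changes the heat herself at the moment the cream is introduced. She cannot take the low ratings that follow as evidence for the cream, because she knows another cause for them.

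What is at stake is the reading of hypotheses 5 and 6. If CI and UI do not differ, the natural conclusion would be that assistant belief has no effect on placebo response or stress. That conclusion requires that the two beliefs were still different during testing, and nothing described in the article would show it. The same analysis is the article's answer to its own limitation about assistants in the room, so that safeguard is also harder to read.

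**Working it through.** No figure in the article decides this point, so the check is a comparison of sections, with one piece of arithmetic on workload.

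1. **Intended belief.** Blinding of assistants: CI is told that all creams are active, UI that half are. Conditioning of assistants: the belief is reinforced with lidocaine for CI only.

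2. **What the assistant then does.** Procedure: the assistant, CI or UI, covertly reduces the stimulus from 5 to 3 after applying the cream. She therefore knows that lower pain in this phase is expected whether or not the cream works.

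3. **Does this contradict the message?** Not logically. An active cream and a reduced stimulus can coexist. The step removes the evidential value of the conditioning ratings for the assistant, and it may lead a CI assistant to wonder why an effective cream needs help. The second part is inference.

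4. **Direction.** Both groups perform the same step. If it erodes belief in the cream, it brings CI closer to UI and pushes the contrast towards zero. It does not by itself create a spurious difference, so a difference in the expected direction would not be undermined on this ground.

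5. **Is there a check?** The Questionnaires section lists participants' expected efficacy but no measure of the assistants' belief. None appears under Research assistants, Blinding of assistants or Statistical analysis.

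6. **How often, and in which role.** Research assistants gives three assistants with 26–28 participants each, so each repeats the step up to 28 times. Half of the planned 80 is 40. One whole assistant gives 26–28 participants and two give 2 × 26 = 52 to 2 × 28 = 56. No whole number of assistants gives 40, so an even CI/UI split requires at least one assistant to serve under both messages. Belief therefore has to be recorded per information condition, not once per assistant.

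7. **Effect on the primary subjective comparison.** Statistical analysis uses post-test minus pre-test. For the calibrated level-5 temperature, Procedure says: "This temperature level is presented in the pre- and post-tests". The reduced stimulus is not part of that score.

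**The case against.** The strongest reply is that the step leaves the manipulation largely in place. The messages still differ (all versus half), only CI assistants have felt lidocaine on their own arm, and lowering the heat tells neither group that the cream is inert. The post-test is run at full heat, so assistants also see the cream under an unreduced stimulus. The hypotheses are exploratory, and assistants' influence is already listed as a limitation. All of this stands, and it is why the erosion is possible rather than shown and the point is minor. It does not supply a belief check, and without one a null result remains ambiguous.

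Three stronger readings are tempting, and the article does not support them.

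- *A reader might infer that level 3 is left to the assistant's judgement, so that conditioning strength depends on who is testing.* The calibration described yields only the level-5 temperature, but no section gives the assistant discretion over level 3. Research assistants describes written instructions, training and a simulation run that must be passed. A rule for the lower level is a detail that a condensed article may leave to the full protocol. Conditioning ratings at 30 s, 2 min and 4 min also give a partial check on the level delivered.
- *A reader might infer that the CI/UI contrast is confounded.* That would require CI and UI assistants to apply different reductions. As written the step is identical, so the threat is dilution.
- *A reader might attach a loss of power to it.* The article's effect size of 0.478 is a placebo versus natural-history difference in pain unpleasantness, not an assistant-belief effect, and any share of it assumed lost would be invented.

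**Conclusion.** The point holds in a limited form. A stated step of the procedure, performed by the assistant herself, works against the belief that two other sections are designed to create, and no measure of that belief is described. A null result on hypotheses 5 and 6 could therefore not be read as showing that assistant belief does not matter. The expected direction is dilution towards no difference, and its size cannot be estimated from the document.

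This rests on two assumptions: that the assistant operates the reduction knowingly, as the Procedure section says, and that the full protocol contains no assistant belief check that the article omits. Severity is minor: the contrast is exploratory, the step is common to both sides, and the pre- and post-test stimuli behind the main subjective outcome are unaffected.

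**What to change.** Reconcile the conditioning step in Procedure with Blinding of assistants and Conditioning of assistants:

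- Run the conditioning and post-test stimuli from a preset sequence on the computer-controlled thermode, started by one neutral command, with the temperature display hidden. The assistant then neither performs nor sees the reduction. The stimulus levels themselves need not change.
- Ask each assistant what share of the creams she believed to be active, separately under each information condition in which she tested, and report the answers alongside hypotheses 5 and 6.

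The question is needed even with the preset sequence. UI assistants who see relief in every participant during conditioning may come to believe that more than half of the creams work, which would also narrow the contrast. If the reduction has to stay manual, the assistants' knowledge of it should be added to Expected limitations.

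The cost is set-up time for the sequence, hiding the display, and one short question per assistant and condition.
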